### Data Management

All study variables will be documented in a secure electronic case report form (eCRF), developed specifically for this protocol and accessible through a dedicated online platform. Data from each participating center will be directly entered by local investigators or study coordinators and automatically transferred to a centralized database.

Each authorized researcher and study monitors will have individual digital access to the eCRF, enabling them to include new patients, update data, and review follow-up entries. All changes or additions in the eCRF system will be automatically logged in an audit trail.

To prevent data loss, monthly backup copies of the database will be generated. The eCRF system and the database will be securely stored and retained for at least 5 years following the study’s completion, with full compliance with GDPR and confidentiality standards equivalent to those used for medical records.

### Statistical Analyses

Statistical analysis will follow the intention-to-treat principle. Descriptive statistics will be employed for summarizing baseline characteristics and perioperative outcomes across the three surgical groups: open, laparoscopic, and robotic.

Univariate analyses (Chi-square or Fisher’s exact test and ANOVA or Kruskal–Wallis test for categorical and continuous variables, respectively) will be performed for comparing outcomes, including complication rates, recurrence, surgical site infections, and hospital length of stay.

To control for potential confounders, multivariate logistic regression models will be applied, particularly for primary outcomes, including postoperative complications (classified using the Clavien–Dindo classification system and Comprehensive Complication Index), hernia recurrence, and chronic postoperative pain.

Time-to-event outcomes (e.g., time to recurrence) will be analyzed using Kaplan–Meier survival curves and compared using log-rank tests. To assess predictors of recurrence or reoperations, Cox proportional hazards models will be employed.

Subgroup analyses will be considered on the basis of patient age, BMI, hernia type (primary vs. recurrent), and surgical approach. P < 0.05 will be considered statistically significant.

To assess data quality, protocol adherence, and recruitment balance across centers, an interim descriptive analysis may be performed following the inclusion of 50% of the expected patient sample.

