## Methods and Design

The SCAR study is a prospective multicenter non-randomized observational cohort study conducted across eight centers in Madrid (Spain) specializing in abdominal wall surgery. The objective is to compare clinical outcomes of inguinoscrotal hernia repairs performed via minimally invasive approaches (laparoscopic or robotic) versus open surgery.

Local approval was necessary for the individual participating centers. Patients eligible to participate in the study will be approached by the investigators and subsequently recorded. All included patients will sign a written informed consent form before study initiation.

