### Inclusion Criteria

• Age ≥18 years;• Diagnosis of inguinoscrotal hernia classified as either S1, S2, or S3 according to the EHS guidelines [11];• Indication for surgical repair performed either electively or in an urgent setting; and• Surgical approach using either open, laparoscopic, or robotic technique according to the standard practice of each center.

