### Sample Size Calculation and Justification

The sample size was calculated to detect clinically significant differences in postoperative outcomes between minimally invasive (laparoscopic or robotic) and open approaches for inguinoscrotal hernias. Specifically, the calculation was based on the hypothesis that minimally invasive approaches would decrease postoperative complication rates by 20% compared with open surgery and lead to a 2-point reduction in postoperative pain (measured using the Visual Analog Scale).

Assuming a 5% significance level (two-sided α) and 80% power (1−β), and accounting for an estimated 5% loss to follow-up, a total of 150 patients (50 per surgical group: open, laparoscopic, robotic) will be required. This sample will enable the detection of statistically and clinically meaningful differences across the three groups using analysis of vairance (ANOVA) or Chi-square tests as appropriate.

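### The named univariate tests treat patients as independent although approach and aftercare follow the center, so the 5% level is not assured, chiefly for early pain, hospital stay and EQ-5D-5L

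*Protocol article*

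**What the plan says.** **Design.** Methods and Design describes a non-randomized cohort in eight Madrid centers. Inclusion Criteria admits a "Surgical approach using either open, laparoscopic, or robotic technique according to the standard practice of each center". Trial-Specific Interventions adds that analgesia, discharge criteria and follow-up are those of each center, and that perioperative data are collected partly to detect variability between centers.

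**Sample size.** "Assuming a 5% significance level (two-sided α) and 80% power (1−β), and accounting for an estimated 5% loss to follow-up", the Sample Size section arrives at 150 patients, 50 in each of three groups, to be compared by ANOVA or chi-square. No allowance for clustering is mentioned.

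**Analysis.** Statistical Analyses names chi-square or Fisher tests for categorical variables and ANOVA or Kruskal–Wallis for continuous ones. These "will be performed for comparing outcomes, including complication rates, recurrence, surgical site infections, and hospital length of stay". Multivariable logistic models follow for complications, recurrence and chronic pain, with no covariates listed. Kaplan–Meier curves with log-rank tests and Cox models are planned for time to event. "P < 0.05 will be considered statistically significant". Centers appear in this section only as an item of recruitment balance in an optional interim look.

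**Outcomes.** VAS pain, length of stay and EQ-5D-5L are all listed as primary under Outcome Measures.

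**The concern.** Two things together make an unclustered test reject too often: outcomes that are alike within a center, and an exposure distributed unevenly across centers. The protocol gives reason to expect both. Analgesia bears directly on VAS, and discharge criteria bear directly on length of stay. Approach is tied to local practice.

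Viewed over the centers that might have taken part, the error rate of the test is above 5%. Viewed within these eight centers, the same problem is confounding by center. Either way, a center with generous analgesia and mainly robotic repair would make robotic repair look less painful. The study hopes to inform guidelines, so a significant result of that kind would matter.

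The sentence naming the univariate comparisons does not list pain. The link to pain comes from the Sample Size section, which builds on a VAS difference and on ANOVA, and from the list of primary outcomes.

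**Working it through.** **1. The plan's own figure.** The 50 per group cannot be uniquely reproduced, because neither the open-surgery complication rate nor the VAS standard deviation is given. It is matched approximately under assumptions (two-sided 5%, 80% power, two groups, loss handled as n/0.95):

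- Complications, 25% vs 5%: n = [1.96·√(2·0.15·0.85) + 0.842·√(0.25·0.75 + 0.05·0.95)]² / 0.20² = 49, and 49/0.95 gives 52.
- Pain, 2 points with SD 3.4: n = 2·(1.96 + 0.842)²·3.4²/2² = 46, and 46/0.95 gives 49.

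Both formulas assume independent patients. Neither contains a design effect.

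**2. Analytic bound.** Suppose each center used one approach. Mean center size is 150/8 = 18.75, and the design effect is 1 + (18.75 − 1)·ICC. The actual two-sided error of a nominal 5% two-group test is 2·[1 − Φ(1.96/√DE)].

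| ICC (assumed) | Design effect | Actual error |
|---|---|---|
| 0.01 | 1.18 | 7.1% |
| 0.05 | 1.89 | 15.4% |
| 0.10 | 2.78 | 23.9% |

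**3. Simulation across mixes.** Inputs from the protocol: eight centers, about 150 patients (144–152 by scenario), three approaches, nominal 5%. Assumed: no true effect, a random center effect, a 25% event rate for the binary outcome, the ICC, and the approach mix. There were 10,000 runs per cell, so the Monte Carlo standard error near 5% is √(0.05·0.95/10,000) = 0.2 percentage points. Entries are three-group ANOVA / three-group chi-square / minimally invasive vs open t-test, in percent, with center ignored.

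| Approach mix | ICC 0.01 | ICC 0.05 | ICC 0.10 |
|---|---|---|---|
| Same in every center | 5.0 / 5.0 / 4.9 | 4.3 / 4.3 / 4.4 | 3.7 / 3.6 / 4.2 |
| Dominant approach about 58% per center | 5.0 / 5.6 / 5.1 | 6.5 / 5.8 / 5.9 | 7.5 / 7.5 / 7.1 |
| Robotic at 3 of 8 centers only | 5.2 / 4.9 / 5.2 | 7.2 / 6.8 / 5.6 | 9.0 / 9.9 / 6.0 |
| Dominant approach about 89% per center | 6.5 / 6.8 / 5.9 | 15.0 / 15.5 / 12.4 | 25.0 / 25.3 / 17.9 |
| One approach per center | 8.3 / 7.9 / 7.3 | 21.5 / 21.9 / 15.9 | 36.2 / 36.4 / 23.5 |

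At ICC 0 all three tests gave 4.5–5.6%. The t-test in the last row (7.3, 15.9, 23.5%) agrees with the analytic values in step 2.

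**4. Does a center term repair it?** For the continuous outcome, an F test with center as a fixed effect returned 4.6–5.3% in every mix where it can be estimated. With one approach per center it cannot be estimated.

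**5. Sparsity.** 150/(8·3) = 6.25 patients per center-by-approach cell on average. At the assumed 25% event rate that is about 1.6 events per cell, and fewer for a rarer event.

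**The case against.** A reader might infer that the 5% level is certainly missed. The documents do not support that. Inflation needs both a non-zero ICC and an uneven mix, and the protocol gives neither. With the same mix everywhere the unadjusted tests are slightly conservative. At ICC 0.01 they stay near 5% unless approach is nearly fixed by center. Nothing says that any center uses only one approach, and repair is also said to depend on surgeon expertise, which leaves room for variation within a center.

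A reader might also infer that every planned analysis ignores center. That holds for the univariate tests and the log-rank test as named. It does not hold for the logistic and Cox models, whose covariates are not listed. The stated aim of controlling confounders, and the remark about variability between centers, leave room for center among them. A condensed article may properly leave that list to an analysis plan.

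Both points stand and narrow the concern. What they do not answer is early VAS, length of stay and EQ-5D-5L. The adjusted analysis is logistic, and the examples given for it do not include these outcomes. The phrase about primary outcomes might be stretched to cover them, but no cut-off is given that would make them binary. For these outcomes the tests that the article does name are unadjusted.

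**Conclusion.** The point holds as a loss of assurance. The article commits to tests that need independent patients, in a design whose own description makes independence doubtful, and names no center-adjusted analysis for three of its primary outcomes. For complications, recurrence and chronic pain the point is weaker: the adjusted model exists, and its handling of center is open.

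The size depends on ICC and mix, both assumed here. For the three-group tests over ICC 0.01–0.10, the actual error is about 4–5% with equal mixes, 5–10% with robotic repair at three of eight centers, and 8–36% with one approach per center. The last range marks the upper end of the scenarios examined and is not a forecast. For the two-group contrast of minimally invasive against open repair, the inflation is smaller in the uneven mixes examined: 5.2–6.0% in the three-of-eight scenario.

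**What to change.** In Statistical Analyses:

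- Make the primary comparison for VAS, length of stay and EQ-5D-5L a linear or ordinal regression on approach with a center effect.
- Name center in the logistic models for complications, using a random effect or a penalised model where events are sparse.
- Stratify the log-rank and Cox analyses by center where the number of events allows.
- Report the center-by-approach table. State that centers using one approach add no within-center information, and that approach and center effects cannot be separated if approach is nearly fixed by center.

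In Sample Size Calculation and Justification, state that the 5% level and 80% power assume independent patients.

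No new data are needed: the Data Management section has records entered by each center's own staff. The cost is wider intervals and little contribution from single-approach centers. The remedy has a limit. If each center used one approach, fixed effects and stratification would give no estimate, and a random-effect model would be a comparison between eight centers. The publication would then have to say so.

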## Main and Secondary Hypothesis

We hypothesize that minimally invasive approaches—both laparoscopic and robotic—will lead to better early postoperative outcomes compared with open repair in patients with inguinoscrotal hernias. Specifically, we expect lower rates of surgical site infections and overall complications (as graded by the Clavien–Dindo classification), reduced postoperative pain as measured by the Visual Analogue Scale, and shorter hospital stays.

We also hypothesize that these advantages will translate into an improved early health-related quality of life, as assessed through the EQ-5D-5L questionnaire.

Regarding long-term results, we hypothesize that minimally invasive repair may be associated with lower rates of chronic pain and better long-term quality of life compared with open surgery.

Additionally, we expect that recurrence rates at 2 years will not significantly differ between minimally invasive and open approaches, reflecting comparable long-term durability of the repair.

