### Trial-Specific Interventions

This is a pragmatic observational study with no imposed modifications to the standard surgical techniques employed at participating institutions. Each center will perform inguinoscrotal hernia repair on the basis of their routine clinical protocols and surgeon expertise.

Open group: may encompass anterior (Lichtenstein) or preperitoneal approaches, with mesh use and fixation technique determined by the operating surgeon.

Laparoscopic and robotic group: comprises TAPP or TEP techniques.

No restrictions regarding mesh type or fixation method are imposed; however, all intraoperative details (mesh type, fixation, use of drains, surgical time, and conversion) will be recorded for future analysis. Surgeons are anticipated to have completed their learning curve in the selected approach. Postoperative management, including analgesia, discharge criteria, and follow-up, will follow each center’s standard practice. This pragmatic approach ensures the study reflects real-world clinical scenarios and facilitates generalizability of the findings. To identify any variability between centers and detect potential confounders, all perioperative data will be systematically collected.

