### Outcome Measures

Primary outcomes:The primary outcomes of this study encompass the postoperative outcomes.-Surgical site infection and surgical site occurrence will be analyzed, and general complication will be assessed and graded using the Clavien–Dindo classification system.Surgical site occurrence (SSO) was defined as any wound-related complication within 30 days after surgery, including both infectious and non-infectious events. SSO included seroma, hematoma, wound dehiscence, and SSI.Surgical site infections (SSI) were assessed within 30 days after surgery. SSI were classified as superficial, deep, or organ/space infections. Superficial SSI involved the skin and subcutaneous tissue, while deep SSI involved the fascia or muscle layers. Organ/space SSI referred to infections involving anatomical structures manipulated during surgery other than the incision.-Postoperative pain will be evaluated using the VAS.-The length of hospital stay will be recorded for all patients as a key marker of recovery.-Furthermore, the assessment of health-related QoL using the QoL questionnaires EuroQol EQ-5D-5LTM will continue.-Return to normal daily activitiesSecondary outcomes:The secondary endpoints will focus on long-term outcomes.-Evaluation of hernia recurrence-Chronic pain and health-related QoL will be assessed at long-term follow-up intervals.

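### Length of stay, a primary outcome, is assigned only an unadjusted test, with no adjusted duration model named for it, although surgical approach and discharge both follow center practice

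*Protocol article*

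**What the plan says.** Outcome Measures lists stay among the primary outcomes: "The length of hospital stay will be recorded for all patients as a key marker of recovery". Main and Secondary Hypothesis gives the expected direction for minimally invasive repair: "reduced postoperative pain as measured by the Visual Analogue Scale, and shorter hospital stays".

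Statistical Analyses names stay once, in the sentence on univariate tests, which "will be performed for comparing outcomes, including complication rates, recurrence, surgical site infections, and hospital length of stay". For a continuous variable these are ANOVA or Kruskal–Wallis across open, laparoscopic and robotic repair. Confounding is handled in the next sentence: "To control for potential confounders, multivariate logistic regression models will be applied, particularly for primary outcomes, including postoperative complications". The outcomes it goes on to name are complications, recurrence and chronic pain. On Cox models it says: "To assess predictors of recurrence or reoperations, Cox proportional hazards models will be employed".

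Methods and Design describes a non-randomized cohort in eight centers. Under Inclusion Criteria the approach is whatever is usual at the center. Under Trial-Specific Interventions, "Postoperative management, including analgesia, discharge criteria, and follow-up, will follow each center’s standard practice".

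Center differences are mentioned twice: "To identify any variability between centers and detect potential confounders, all perioperative data will be systematically collected" (Trial-Specific Interventions) and "To assess data quality, protocol adherence, and recruitment balance across centers, an interim descriptive analysis may be performed" (Statistical Analyses).

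**The concern.** By the protocol's own description, center can influence both the exposure (which operation) and the outcome (when the patient goes home). That makes it a potential confounder of the comparison of stay. Stay is more exposed to this than, say, wound infection, because the discharge date is partly a matter of local routine.

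If the centers that do more laparoscopic or robotic repairs also discharge earlier by habit, Kruskal–Wallis can credit the operation with what is really discharge policy. If those centers discharge later, a real benefit can be hidden. Randomization would protect against this; here only the analysis can. The analysis named for stay does not adjust, and the adjusted model named for primary outcomes does not naturally take a duration.

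**Working it through.** **Text check.** In Statistical Analyses, stay appears under univariate tests only. The adjusted sentence offers logistic regression, which would need stay to be dichotomized, and no cut-off is given. Cox is assigned to other outcomes. No linear, count, log-linear or mixed model is named for stay, and no center term.

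**Inputs from the protocol.** 50 patients per group and 5% loss: 50 × 0.95 = 47.5, taken as 47, so 3 × 47 = 141 evaluable. Eight centers, three approaches, two-sided 5% level. The plan gives no figure for stay to reproduce.

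**Assumed, because the protocol gives no values.** Four early-discharge and four late-discharge centers. Stay = 1 + exponential (mean 1) nights, plus a gap in late centers. No true effect of approach. The mix is the share of minimally invasive v open patients treated in early-discharge centers.

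**Spurious difference in mean stay.** Gap × (late-center share in open − late-center share in minimally invasive). With a 0.5-night gap:
- 50/50: 0.5 × (0.5 − 0.5) = 0
- 70/30: 0.5 × (0.7 − 0.3) = 0.20 night
- 80/20: 0.5 × (0.8 − 0.2) = 0.30 night

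**False-positive rate of unadjusted Kruskal–Wallis**, 2,000 simulated trials per setting (Monte Carlo standard error near 5%: √(0.05 × 0.95 / 2000) ≈ 0.5 points):

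| Gap and recording | 50/50 | 60/40 | 70/30 | 80/20 |
|---|---|---|---|---|
| 0.1 night, continuous | 4.4% | 4.5% | 6.6% | 6.2% |
| 0.25 night, continuous | 5.1% | 6.1% | 10.4% | 19.8% |
| 0.25 night, whole nights | 6.2% | 5.3% | 6.7% | 8.6% |
| 0.5 night, continuous | 4.3% | 9.8% | 26.3% | 53.6% |
| 0.5 night, whole nights | 4.8% | 7.4% | 13.4% | 26.2% |
| 1 night, continuous | 4.9% | 15.9% | 58.5% | 93.8% |
| 1 night, whole nights | 4.0% | 19.4% | 65.3% | 96.9% |

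Rounding matters. At 80/20 with a 0.5-night gap, whole nights give about 26% if fractions are always cut off or always rounded up, but about 60% if stay is rounded to the nearest night. A rank-based F test with an eight-level center term rejects in 4.2–6.2% of runs in every setting.

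**Other outcome models.** If centers differ in day-case rate instead, the unadjusted rate at 80/20 is 8.1% (55% v 45% day cases), 18.4% (60% v 40%) and 63.8% (70% v 30%); with a center term it is 4.3–5.9%. In a separate log-normal model (150 patients, residual SD 0.6 on the log scale, mix varying freely by center), between-center SDs of 0, 0.25, 0.5 and 0.75 give 5.5%, 17%, 30% and 41% unadjusted, against 4–5% with center.

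**Masking.** True benefit 0.5 night, minimally invasive repairs mostly in late-discharge centers (continuous stay):
- Gap 0.25, 80/20: the mean difference shrinks to 0.5 − 0.25 × 0.6 = 0.35 night. Power is 74% unadjusted, 83% with center.
- Gap 0.5, 80/20: 23% v 78%.
- Gap 0.25, 90/10: 60% v 57%, so the center term no longer helps.
- Gap 0.1, 80/20: 91% v 83%, so it costs more than it gains.

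**Price of the center term** (benefit 0.5 night, no gap). Unadjusted power is 96–97% throughout. With center it is 96% at 50/50, 91% at 70/30, 82% at 80/20, 56% at 90/10 and 36% at 95/5. Average cell size is 141 / (8 × 3) = 5.9 patients.

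**The case against.** The strongest reply is that a condensed article leaves covariates and model form to a fuller document. The adjusted sentence is open-ended and stay is a primary outcome, so it may be covered. No covariates are listed for any outcome, so the absence of center is silence, not exclusion. The stated aim of detecting confounders may well feed the adjusted models. This stands against any inference that the plan rules out adjusting stay or ignores centers; the text does not support that. It does not remove the point, because the article does fix methods. Stay gets a univariate test, and reading it into the adjusted sentence gives it a model that does not fit a duration.

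A reader might also infer that Cox regression is unsuitable. It is not: it can model time to discharge, and the mention of time-to-event outcomes gives recurrence only as an example. The accurate statement is that the plan assigns Cox elsewhere.

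The size is wholly assumed. All eight centers specialize in abdominal wall surgery in one city, so discharge habits may be similar and the bias negligible. It is tempting to say the false-positive rate exceeds 50% at 80/20 with a 0.5-night gap, but that depends on how stay is recorded.

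Two further objections stand. Adjustment is weakest where confounding is worst, since centers that use one approach contribute little within-center comparison. And stay is not special: pain on the VAS, EQ-5D-5L and return to activities are also primary outcomes that logistic regression does not naturally fit, and the VAS, unlike stay, enters the sample size.

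**Conclusion.** The point holds in this form: a primary outcome with a predicted direction has only an unadjusted comparison named for it, no adjusted model suited to a duration is named, and the protocol makes center a possible common cause of approach and discharge. The bias can go either way.

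Its size is unknown until the center-by-approach mix and the discharge gaps are seen. The simulated rates, from nominal at an equal mix or very small gap to roughly 25–60% at 80/20 with a 0.5-night gap, rest on an invented stay distribution and a two-policy split of centers. They show a range, not a forecast. The change should be made, but it does not undermine the study as a whole.

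**What to change.** In Statistical Analyses, add for length of stay an adjusted analysis suited to a duration: for example a log-linear, count or rank-based regression on approach, or a Cox model for time to discharge. Include center as a stratum or fixed effect, the variables under Patient Baseline Characteristics (age, sex, BMI, ASA status, Charlson index, hernia type and classification), and elective or urgent status. Urgent repairs are eligible and urgency could affect both approach and stay, but it is not in the article's variable lists, so confirm that the eCRF records it. Fix the model before results are seen.

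Report the adjusted result beside the unadjusted test, with a table of patients by center and approach. Do not claim faster recovery from the unadjusted difference alone. Where few centers use more than one approach, call the adjusted result inconclusive. Name adjusted models of the same kind for the VAS, EQ-5D-5L and return to activities.

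The cost is a few sentences and one table, almost entirely from data already planned, plus the loss of precision shown above: small with a balanced mix, severe when centers concentrate on one approach. That is why the adjusted result should accompany the unadjusted test and not replace it.

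### The only method stated for controlling confounding, logistic regression, does not fit the continuous and duration primary outcomes, and centre enters no comparative analysis

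*Protocol article*

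**What the plan says.** The Protocol article describes a prospective, non-randomised cohort in eight Madrid centres (Methods and Design).

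- **How approach is set.** The Inclusion Criteria require "Surgical approach using either open, laparoscopic, or robotic technique according to the standard practice of each center". Trial-Specific Interventions adds: "Each center will perform inguinoscrotal hernia repair on the basis of their routine clinical protocols and surgeon expertise".
- **How aftercare is set.** "Postoperative management, including analgesia, discharge criteria, and follow-up, will follow each center’s standard practice" (Trial-Specific Interventions).
- **Primary outcomes.** Outcome Measures lists surgical site events and Clavien–Dindo complications, VAS pain, length of stay, EQ-5D-5L and return to daily activities. Postoperative Data records sick leave as a number of days until return to work or daily activities. Table 1 schedules VAS and quality of life at baseline and at several later visits.
- **Unadjusted tests.** Under Statistical Analyses, Chi-square or Fisher tests and ANOVA or Kruskal–Wallis tests "will be performed for comparing outcomes, including complication rates, recurrence, surgical site infections, and hospital length of stay".
- **Confounder control.** The same section says "multivariate logistic regression models will be applied, particularly for primary outcomes, including postoperative complications". It goes on to name recurrence and chronic postoperative pain, both of which are secondary in Outcome Measures.
- **Other models.** Kaplan–Meier curves with log-rank tests for time-to-event outcomes, and Cox models for predictors of recurrence or reoperation.
- **Centre.** "To identify any variability between centers and detect potential confounders, all perioperative data will be systematically collected" (Trial-Specific Interventions). In Statistical Analyses, centre appears only in an optional interim descriptive check of recruitment balance.

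**The concern.** Without randomisation, the difference between approaches is interpretable only after adjustment. The protocol accepts this and names a model for the purpose, one for binary outcomes. Four of the primary outcomes are scores, repeated measures or durations, and one of them, VAS pain, is a basis of the sample size. If the plan is followed as written, these outcomes are either compared crudely or cut at an unstated threshold.

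Centre makes this concrete. By the protocol's own account, centre practice influences which operation a patient receives, and it also sets analgesia and discharge criteria, which bear directly on pain and hospital stay. A shorter stay after minimally invasive repair could therefore reflect the discharge practice of the centres that favour it. A crude test would report that as an effect of approach, with a standard error that ignores clustering.

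**Working it through.** **Step 1: match each primary outcome to the stated methods.**

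| Primary outcome | Scale | Unadjusted test | Stated method for confounding |
|---|---|---|---|
| Complications | binary or graded | named | logistic regression, named |
| Surgical site infection | binary | named | logistic regression fits; not named separately |
| Early VAS pain | score, repeated, with baseline | not named; falls under an open list | none that fits |
| Hospital stay | duration | named | none that fits |
| EQ-5D-5L | score, repeated, with baseline | not named; falls under an open list | none that fits |
| Return to activities | days | not named; ANOVA/Kruskal–Wallis or log-rank | none that fits |

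No linear, mixed, count or propensity method appears. No stated analysis includes, stratifies by or clusters on centre.

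**Step 2: size of the centre problem.** The plan has no figure of its own to reproduce here: it gives neither an intraclass correlation (ICC) nor the mix of approaches within centres. Both are assumptions below.

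*Worst case, approach fully aligned with centre.* With 150 patients in 8 equal centres, m = 150/8 = 18.75. The design effect is DE = 1 + (m − 1) × ICC = 1 + 17.75 × ICC. The true two-sided error of a nominal 5% test is 2 × [1 − Φ(1.96/√DE)].

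| ICC | DE | Effective N (150/DE) | True error |
|---|---|---|---|
| 0.01 | 1.18 | 127 | 7.1% |
| 0.02 | 1.36 | 111 | 9.2% |
| 0.05 | 1.89 | 79 | 15.4% |
| 0.10 | 2.78 | 54 | 23.9% |

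*Partial alignment, by simulation.* Inputs: 8 centres of 18 patients, 5 leaning to minimally invasive and 3 to open repair, a normal outcome, no true effect, a crude two-group t-test at 5%, and 60,000 runs per cell (Monte Carlo standard error at most 0.2 percentage points).

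| Mix within centres | ICC 0.01 | 0.02 | 0.05 | 0.10 |
|---|---|---|---|---|
| 50/50 | 5.0% | 5.1% | 5.0% | 5.0% |
| 67/33 | 5.1% | 5.3% | 6.2% | 7.4% |
| 80/20 | 5.8% | 6.4% | 8.7% | 12.2% |
| Fully aligned | 7.2% | 9.0% | 15.2% | 23.6% |

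The last row agrees with the formula. The inflation is negligible when centres mix approaches evenly and serious when each centre mostly uses one.

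**Step 3: size of patient-level confounding, as illustration.** Take 50 per group less 5% loss, so 50 × 0.95 = 47.5. Assume a binary prognostic factor worth 2 VAS points, no true effect, and an SD of 2 to 3. Bias = prevalence gap × 2, and SE = SD × √(2/47.5), which is 0.41 to 0.62. The crude test rejects with probability Φ(bias/SE − 1.96) + Φ(−bias/SE − 1.96).

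| Prevalence gap | Bias (VAS points) | False positives, SD 3 to SD 2 |
|---|---|---|
| 10 points | 0.2 | 6–8% |
| 20 points | 0.4 | 10–16% |
| 30 points | 0.6 | 16–31% |

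If the factor is worth only 1 point, the rates are about 5–6%, 6–8% and 8–11%.

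**The case against.** The strongest reply is that covariate lists, a centre term, use of baseline values and repeated-measures models normally belong in an analysis plan, which may exist and is not shown. That stands for those details, and their absence alone would be no finding. It does not cover the choice the article does make: it names one model for confounding, directs it at the primary outcomes in particular, and that model does not suit four of them.

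Several stronger readings are tempting, and the documents do not support them:

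- *Logistic regression is the only regression planned.* Cox models are also named. They are for predictors of recurrence or reoperation, so they do not help these four outcomes.
- *All four outcomes are assigned crude tests.* Only hospital stay is. The method lists are open-ended, so VAS, EQ-5D-5L and return to activity are unassigned rather than expressly left crude.
- *Pain is never adjusted.* Chronic pain is named for logistic regression; the gap is early VAS pain.
- *Complications are mismodelled because the Comprehensive Complication Index is mentioned.* A binary complication outcome suits logistic regression, and the text can be read that way.
- *Surgeons select by hernia size or comorbidity.* This is plausible, but the protocol cites only centre practice, routine protocols and surgeon expertise.
- *Intraoperative variables will be adjusted for.* The protocol says they are collected to detect confounders, not that they enter a model.

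The protocol does intend to look at variability between centres. That is a reason for collecting data; no analysis follows from it.

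**Conclusion.** The concern holds in this form: for early VAS pain, hospital stay, EQ-5D-5L and return to activity, no suitable confounder-adjusted analysis is stated, hospital stay is expressly tested crudely, and centre is in no comparative analysis although the protocol links it to both approach and aftercare. This part rests on the text alone.

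The size is conditional. For ICCs of 0.01 to 0.10, the true error of a crude 5% test is about 5–7% with a 50/50 to 67/33 mix, 6–12% at 80/20, and 7–24% under full alignment. A reader might take the upper figures as this study's error rate. They are not: the documents give neither the ICC nor the mix, and the calculation uses two groups and a normal outcome. Patient-level confounding would come on top, by an amount the documents do not allow one to estimate.

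**What to change.** In Statistical Analyses, make a confounder-adjusted estimate the main comparison for each of the four outcomes and keep the univariate tests as descriptive:

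- **VAS and EQ-5D-5L:** a linear mixed model over visits (or a linear model at one named visit) with the baseline value as covariate.
- **Hospital stay and return to activity:** a time-to-event or count model.
- **Covariates:** one preoperative set that is already collected (hernia type and EHS class, age, BMI, ASA, Charlson), plus elective or urgent setting. The Inclusion Criteria allow both settings, but the listed baseline variables do not name this one.
- **Centre:** a random effect or stratification in every comparative model, including the logistic ones.
- **Reporting:** a table of approach by centre.

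The cost is wording, modest programming and some precision. There is also a limit to state openly. A centre that uses only one approach gives no within-centre contrast under a fixed centre effect or stratification, and if every centre does so the approach effect cannot be separated from centre at all. A random effect then corrects the standard error but does not remove confounding by centre. The approach-by-centre table shows how far this applies.
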